### Sample size

We conducted a power analysis using Proc Power in SAS for our primary outcome variable, maximum strength. We used the standard deviation of 48 lbs. observed in our pilot study and assumed that maximum strength will remain unchanged in the waiting list control group. A total sample size of 82 participants, with 41 per group, provides 90% power to detect at least a 20% difference in mean change between groups at a 0.05 level of significance. In another clinical trial conducted by the investigative team at this site, we observed 23% missing data at week 2 and 29% at week 4 [56]. Therefore, we increased the sample size to 110, with 55 per group, to account for the possibility of a 25% dropout rate.

### Internal quality assurance

Data management and quality control of data entered into web forms are performed using SQL views, stored procedures, and real-time web-based reports. Automated reports are viewed by the data core manager and PMs and guide the need for improved documentation, protocol revisions, or personnel retraining, and to track recruitment and participant accrual.

The lead PM audits the trial site quarterly. Audit procedures are designed to maintain data integrity and ensure protocol fidelity. The lead PM reviews regulatory and informed consent documents. Paper documents are verified against electronic data entered into STaRS. Errors discovered are documented, corrected, and reported to the PI, collaborating investigators, and appropriate regulatory bodies when applicable. Site visits also include meetings with the site PI and chiropractor to facilitate communication, discuss timelines, and address concerns. Key information from site visits is communicated to co-investigators by the lead PM.

### Study event monitoring and reporting

#### Study events

Study events are classified into three categories: (1) protocol deviations, (2) protocol violations, and (3) unanticipated events. A protocol deviation is any variance in the approved trial protocol, criteria, or procedures that does not affect a participant’s safety, rights, or welfare or the integrity of the trial and its resultant data. Protocol violations are deviations that increase risk, decrease benefit, or affect a participant’s rights, safety, or welfare or the integrity of the resultant data. Events that do not meet the above definitions but may affect a participant’s rights, safety, or welfare or the integrity of the resultant data are classified as unanticipated events.

All study events are entered into STaRS by trial personnel. The lead PM and PI receive an automatic email notification when a study event is submitted. These individuals are responsible for classifying the event and reviewing its details to ensure proper reporting. Submission of information on study events to an IRB is dictated by the reporting requirements for each IRB overseeing the trial. Deviations that may affect the safety or rights of participants, or the integrity of the trial, are promptly reported to the DSMC and the U.S. Army Medical Research and Material Command Human Research Protection Office.

#### Adverse events

An adverse event is any untoward medical occurrence that happens during the conduct of the trial and which may have a causal relationship with a trial procedure [57]. A serious adverse event is any adverse experience occurring during the trial period that results in any of the following outcomes: death, a life-threatening adverse experience, hospitalization or prolongation of existing hospitalization, a persistent or significant disability or incapacity, or a congenital anomaly or birth defect. We monitor adverse events from when consent is signed until the final visit.

The PM inquires about adverse events weekly via telephone. Participants are also instructed to contact the PM if they experience significant pain, discomfort, or distress that they believe may be associated with treatment. Adverse event reports are electronically documented and submitted by the PM through STaRS. The lead PM and central trial clinician receive an automatic notification email for each adverse event report. The central trial clinician classifies adverse events, which are then reviewed by the lead PM. Classification occurs on three levels: (1) seriousness, (2) expectedness, and (3) relatedness. Following adjudication, adverse events meeting IRB reporting criteria are reported to each relevant IRB. Additionally, all adverse events that may affect the safety or rights of volunteers are reported to the DSMC and the U.S. Army Medical Research and Material Command Human Research Protection Office as required. Events not meeting the criteria for reporting are submitted to the IRBs at the next review or otherwise as required.

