### Waiting list

Participants allocated to the waiting list group are asked to avoid chiropractic treatment or SM by any other provider within or outside the military health system during the active trial period. Participants in this group are scheduled for one additional visit 4 weeks (±7 days) after allocation. Waiting list group participants may receive any other care available to them. All treatment obtained for LBP during this trial is documented via participant self-report and confirmed through review of their military medical record. After trial completion, waiting list group participants are offered the option to be scheduled for CC. Care provided beyond this time is not part of the trial and no data are collected. During weeks 1–3, the PM contacts each participant (both groups) weekly to track treatments for LBP and to screen for adverse events.

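### The adverse-event definition requires a possible causal link to a trial procedure, which conflicts with the later relatedness step and the serious-event definition and may bias event counts by arm

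*Protocol article*

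**What the plan says.** All the key statements are in the Adverse events section of the protocol article.

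- **Adverse event.** "An adverse event is any untoward medical occurrence that happens during the conduct of the trial and which may have a causal relationship"; the sentence goes on to specify that the relationship is with a trial procedure.
- **Serious adverse event.** "A serious adverse event is any adverse experience occurring during the trial period that results in any of the following outcomes". A list of outcomes follows, with no causal condition.
- **Classification.** The central trial clinician classifies submitted reports: "Classification occurs on three levels: (1) seriousness, (2) expectedness, and (3) relatedness".
- **Spontaneous reports.** "Participants are also instructed to contact the PM if they experience significant pain, discomfort, or distress that they believe may be associated with treatment".
- **Window.** "We monitor adverse events from when consent is signed until the final visit".

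Other sections complete the picture. Under Waiting list, in weeks 1 to 3, "the PM contacts each participant (both groups) weekly to track treatments for LBP and to screen for adverse events". Under Trial organization, the site PM records adverse events. Under Allocation, the same person runs the allocation module and tells participants their group. Under Data and safety monitoring committee, the committee reviews adverse-event data twice a year and may recommend that the trial continue, stop or change.

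**The concern.** Possible causality is a condition of entry, and relatedness is then judged as though it were still open. An event that the recorder considers to have no possible link to a procedure is not an adverse event by definition, so no report is called for and the central clinician need never see it. Part of the relatedness decision thus moves from a central role to a site role that knows the allocation.

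The condition also does not bear equally on the two arms. During the four weeks, chiropractic care participants receive repeated trial treatment and waiting-list participants do not. The same back-pain flare in week 2 has an obvious candidate cause in one arm and a much weaker one in the other. At stake are any adverse-event table by arm and the committee's ability to set events under chiropractic care against a background rate.

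**Working it through.** The protocol gives no adverse-event rate, count, margin or test, so there is no stated figure to reproduce. The check is a comparison of texts, followed by an illustration on assumed inputs.

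**1. Adverse-event definition against the relatedness step.** The definition admits an event only if a causal link is possible. The classification then grades relatedness. If the first is applied as written, the lowest grade of the second (no possible relation) should be empty, because such events were never admitted. Either the definition or the grading is not meant as it stands.

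**2. Adverse-event definition against the serious-event definition.** Take a hospitalization plainly unconnected with any trial procedure. It meets the serious-event definition, which carries no causal condition, and fails the adverse-event definition. Yet seriousness is a level assigned to submitted adverse-event reports. The two definitions do not nest.

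**3. Who applies the screen.** The site PM makes the weekly calls, documents events and submits the reports. The central clinician is notified once a report exists. A threshold at capture is therefore applied by someone who knows the arm. The scripts and checklists described under Trial limitations concern the strength, balance and endurance tests.

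**4. Which procedures each arm undergoes, and when.**

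- Before allocation: both arms do the balance, strength and endurance tests at the second baseline visit.
- Allocation to final visit: the chiropractic care arm has treatment visits. The waiting list has only the weekly calls, so an event there can be tied to a procedure only as an after-effect of baseline testing.
- Final visit: both arms repeat the tests, after the safety check, at the visit where monitoring ends. Only immediate reactions fall inside the window.

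The definition therefore admits post-allocation events more readily in the chiropractic care arm. The spontaneous-report instruction leans the same way, since waiting-list participants receive no trial treatment with which to associate a symptom.

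**5. Illustration.** Take *n* = 55 per arm (Sample size section). Assume an equal true all-cause event risk *p* in both arms and capture shares *a*(CC) and *a*(WL) for chiropractic care and the waiting list. Only *n* comes from the protocol.

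- Captured events in an arm = 55 × *p* × *a*
- Spurious difference in risk = *p* × (*a*(CC) − *a*(WL))

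Results:

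- Shares 50% and 50%: difference 0 at any *p*.
- Shares 50% and 25%, *p* = 10%: 2.75 against 1.375 events; 0.10 × 0.25 = 2.5 percentage points.
- Shares 50% and 25%, *p* = 30%: 8.25 against 4.125 events; 0.30 × 0.25 = 7.5 points.
- Shares 75% and 25%, *p* = 10%: 4.125 against 1.375 events; 0.10 × 0.50 = 5 points.
- Shares 75% and 25%, *p* = 30%: 12.375 against 4.125 events; 0.30 × 0.50 = 15 points.

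The result is driven by the gap between the two capture shares, and the documents say nothing about its size.

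**The case against.** The strongest reply is that this is a drafting inconsistency with limited reach. Several parts of that reply stand.

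- *May* is a permissive threshold. No sentence tells the PM to discard events, and relatedness is formally assigned to the central clinician. A cautious recorder would submit nearly everything.
- The qualifier refers to any trial procedure, not to chiropractic care alone. Both arms do the same maximal-effort tests, which the eligibility table treats as a safety matter. Both also have the same weekly calls and monitoring window.
- The serious-event definition on its own wording admits unrelated events. The Study events section adds a category of unanticipated events that may catch some occurrences, although these are classified by the lead PM and principal investigator.
- Worsening back pain in controls is not invisible: treatments for it are tracked in both groups, and pain and disability are measured at the final visit.

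A reader might infer more: that the waiting list can hardly generate events, so that the safety comparison is invalid. The documents do not support this. The shared tests, calls and window contradict the first part. As to the second, the Specific Aims and Statistical methods sections state no between-arm safety analysis. A large figure is also tempting: an assumed 15% flare rate would give 55 × 0.15 = 8.25 events against none, a 15-point excess. That requires 100% capture in one arm and 0% in the other, and nothing in the protocol indicates either.

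The reply does not remove the contradiction. The causal condition is a stated rule rather than omitted detail, and it cannot be applied together with the other two statements as written.

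**Conclusion.** The point holds as an inconsistency within the Adverse events section, with a risk of bias attached. The adverse-event definition, the serious-event definition and the relatedness step cannot all be followed literally. If the definition is followed, an unblinded site role screens for causality first, and post-allocation events enter more easily under chiropractic care. Any tabulation by arm and the monitoring committee's data may then be biased.

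The size is unknown. The 0 to 15 points shown depend on assumed risks and capture shares and are not an estimate. If the PM in practice submits every event, the bias largely disappears and only the wording needs repair. The primary outcome, its analysis and the sample size are untouched. This is a moderate safety-reporting point that should be corrected.

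**What to change.** - Delete the causal qualifier from the adverse-event definition, so that it agrees with the serious-event definition and the relatedness step.
- Record every untoward occurrence in both arms, whatever its suspected cause, through the existing weekly calls and the final visit.
- Ask participants to report significant symptoms without tying the request to treatment.
- Leave the judgement of relatedness wholly to the central trial clinician.

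The cost is a wording amendment and somewhat more event forms; the calls already reach both groups. There is also a cost of timing. The Trial status section gives 93 participants allocated by 8 October 2018, which is 93/110 = 85% of the target, so an amendment would change the capture rule late in the trial. Reports of adverse events should state which rule applied and when. For events collected under the present wording, they should state that a possible causal link was a condition of being counted.

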### Trial limitations

Studies using a waiting list as a control are limited because participants are not blind to group and waiting list participants do not have the same attention given to them as those in an active intervention arm. We chose a waiting list as the control because inert sham treatments for SM procedures involving the low back have not been sufficiently developed to be used widely in clinical trials without participants recognizing the procedure as sham and because clinical outcomes are secondary to objectively measured strength, balance, and endurance. Further, sham treatment was not an available treatment option at this treatment facility, making a waiting list option the only practical and available control group strategy.

CC participants may not receive the same treatment or the same number of visits as each other. This limitation is due to the varied nature of conditions comprising LBP and to scheduling limitations at the health facility. The variation in both treatments and visits likely to be experienced by participants reflects CC as applied in U.S. military health treatment facilities. Thus, the results are more likely to represent the effects of CC as applied in these settings. CC was intended to be provided by a single practitioner. However, this plan was altered shortly after recruitment began. Only two chiropractors provide treatment in this trial, with most care administered by one. The lack of practitioner and participant blinding to group is a limitation common to studies involving manual therapies. The PM functions as the assessor for the strength, balance, and endurance tests. To minimize this limitation, tests are conducted using scripts and checklists to ensure the actions and language are consistent among participants to minimize the possibility of communicating disparately between group members.

### Challenges

There have been several challenges in conducting this trial to date, leading to periods where study activities, including recruitment, were temporarily suspended. One month after recruitment launched in April 2016, the site PI received deployment orders, which led to the suspension of study activity. After a replacement PI was identified and regulatory approval obtained, recruitment resumed in June 2016. In October 2016, enrollment was again suspended when the study chiropractor unexpectedly became seriously ill and passed away. A period of 9 months elapsed before a new chiropractor was able to engage in patient care and recruitment restarted. This lapse consisted of the subcontractor candidate search, interview and hiring process, employee credentialing, and NHP facility-specific training on institutional policies, procedures, and electronic health record use. In addition, the second PI was transferred to another site, resulting in a second temporary suspension lasting until June 2017. This may impact our ability to reach our targeted sample size of 110. However, if this is the case, we do not anticipate an underpowered study because as of 8 October 2018, only 6.1% of participants have withdrawn or dropped out, rather than the anticipated 25% that was used to inflate the necessary sample size to 110.

## Discussion

In this trial, we will evaluate the effects of CC on measures of strength, balance, and endurance, potentially important factors leading to reduced readiness in affected military personnel. These objective measures were chosen because of their potential to help understand how these key aspects of fitness relate to military personnel with LBP and are influenced by CC. Upon completion of this trial, the authors plan to publish the study results in a peer-reviewed journal. Results from this trial may inform further investigations of neuromuscular mechanisms and the potential use of objective measures for assessing clinical improvement for conditions causing LBP.

### Trial status

The first participant was allocated on 26 April 2016. As of 8 October 2018, 93 participants had been allocated. The last allocation is expected to occur in December 2018 followed by a 4-week active trial period.

## Abbreviations

BL1: Baseline visit 1
BL2: Baseline visit 2
CC: Chiropractic care
DSMC: Data safety monitoring committee
IRB: Institutional review board
LBP: Low back pain
NHP: Naval Hospital Pensacola, FL
PCCR: Palmer Center for Chiropractic Research
PI: Principal investigator
PM: Project manager
PROMIS: Patient-Reported Outcomes Measurement Information System
PRO: Patient-reported outcome
RCT: Randomized controlled trial
SM: Spinal manipulation
STaRS: Submission Tracking and Reporting System
